#### Attribute relative importance and probability of opt-out

For each of the sex-class combinations, the relative importance of each attribute will be calculated by dividing the range of the parameter estimates of a given attribute by the summation of the ranges of all attributes.^28^

We will further illustrate potential preference heterogeneities by using equation 2 to calculate the predicted probabilities of selecting ‘opt-out’ over select sexual health service scenarios for each sex-class combination. Specifically, the predicted probability of a participant choosing alternative *i* over alternative *j* can be estimated by dividing the exponentiated summation of coefficients for scenario *i* by the exponentiated summation of coefficients for scenario *j*.

$$\text{Pi}=\frac{e^{\beta x_{i}}}{\sum e^{\beta x_{j}}}$$

Equation 2: Predicted probability of selecting alternative *i* within a two-alternative choice set'.

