### Sample size calculation

Given the absence of any DCE priors for sexual health preferences of older adults in the UK, we used the following parametric-based DCE sample size calculation formula:

$$n\geq \frac{1-p}{rpa^{2}}\times {\left[(\Phi {)}^{-1}⟮1-\frac{\alpha }{2}⟯\right]}^{2}$$

Equation 1: Parametric DCE sample size formula.^26^

Whereby *n* is the minimum sample size needed to detect *p*, the assumed true population probability of selecting uptake of sexual health services over ‘opt-out’, and whereby *r* is the number of choice sets that each individual completes, *a* is the level of precision around the assumed population probability, Ф^−1^ is the inverse cumulative normal distribution function and α is the significance level.^26^ Conservatively assuming that the true population probability of sexual health service uptake is 0.5 and assuming that each participant will complete eight choice sets, we estimate that a sample of 191 participants will be needed to generate a point estimate ±0.05 of the true population probabilities and with 95% confidence. However, to maintain power for two-group subgroup analyses, we will aim to recruit a total 240 participants including those from sexual minorities groups and disabled people.

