### Statistical analysis

We will use descriptive statistics to summarise the key sociodemographic characteristics of the study population. We will assess sexual health service preferences and preference heterogeneity using MNL, latent class and mixed logit (MXL) models. While the MNL is the starting point for most discrete choice models, it suffers from some unrealistic assumptions, particularly around unobserved heterogeneity. The MXL model can accommodate unobserved heterogeneity. The MXL analysis will be conducted with 1000 Halton draws and will assume normally distributed preference heterogeneity for each attribute level. We will assess for unobserved heterogeneity by examining the statistical significance of the SD of the random parameters in the MXL model. We will calculate the relative importance and predicted probabilities of opt-out for select sexual health service scenarios. We will assess how sexual health service and message sharing preferences could vary among those willing and unwilling to use sexual health services by using interaction terms for sociodemographic characteristics.

We will perform latent class analyses to elucidate if there are unobserved groups of people with similar preferences for use of sexual health service.^27^ First, we will conduct a latent class conditional logit model that includes individual characteristics and attribute level preferences.^27^ Selection of individual characteristics will be determined by expert opinion and findings from the formative qualitative interviews. Second, we will determine the optimal number of subgroups by comparing the Bayesian information criterion (BIC) values of 2, 3, 4, 5, 6 and 7-class models and each models’ interpretability and class size distribution.^27^ Lower BIC values indicate better model fit. Third, we will use descriptive statistics to characterise each class based on their members’ preferences and characteristics. All analyses will use effects coding and be weighted to reflect the population of middle-aged and older adults in the UK.

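### The relative-importance score is a range of estimates, so attributes with no effect get a positive expected score and group comparisons partly reflect group size

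*Protocol article*

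**What the plan says.** The section headed Attribute relative importance and probability of opt-out fixes both the formula and the unit. The unit is the sex-by-class cell: "For each of the sex-class combinations, the relative importance of each attribute will be calculated". The formula is "calculated by dividing the range of the parameter estimates of a given attribute by the summation of the ranges of all attributes". The same section then uses predicted opt-out probabilities for the same cells as a further illustration of differing preferences, so the cell-level scores are meant to be compared between groups.

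Under Statistical analysis, the number of latent classes is to be chosen by "comparing the Bayesian information criterion (BIC) values of 2, 3, 4, 5, 6 and 7-class models", together with how interpretable the classes are and how people are spread over them. That section also says "All analyses will use effects coding and be weighted to reflect the population of middle-aged and older adults in the UK". It does not say how sex enters the latent class model.

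Under Sample size calculation, "we will aim to recruit a total 240 participants". The number comes from the precision of one uptake probability, raised to allow two-group subgroup analyses. It was not derived from the precision of attribute coefficients within classes or sex-class cells.

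**The concern.** The score takes the largest minus the smallest estimated level coefficient. If an attribute has no effect, its true range is zero, but its estimated range is almost surely above zero because the level estimates differ by chance. This is not noise that averages out: the expected score is positive. Since the scores in a cell sum to 1, what null attributes gain is lost, on average, by the strong ones.

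The amount depends on standard errors, hence on group size. Two groups with the same true preferences but different sizes have different expected scores. A reader would see flatter importance in the smaller group and could take it for a real difference in what that group wants. The study is meant to help tailor services, so apparent importance that comes from sampling error could direct attention to features that do not matter to users.

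**Working it through.** **The plan's own figure.** The article gives no expected value for the importance score. Its one reproducible figure is the sample size. Equation 1 with p = 0.5, r = 8, a = 0.05 and z = 1.96 gives (0.5 / (8 × 0.5 × 0.0025)) × 3.8415 = 50 × 3.8415 = 192.07, so 193 when rounded up. The article states "we estimate that a sample of 191 participants will be needed". The two agree closely, and the difference does not bear on this point.

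**Group sizes.** With 240 people, two sexes and K classes, the average sex-class cell has 240/(2K) people: 60, 40, 30, 24, 20 and 17 for K = 2 to 7. If coefficients are shared across sexes, the effective unit is the class, 240/K: 120 for K = 2 down to 34 for K = 7.

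**Why the bias depends on size.** Take a two-level effects-coded attribute with estimate b for one level and −b for the other. The estimated range is 2|b|. If the true value is 0 and b is normal with standard error s, the expected range is 2s√(2/π), about 1.6s, which is above zero. As s falls with 1/√n, the expected null range doubles from n = 240 to n = 60 (√(240/60) = 2). The share grows a little more slowly because the denominator is also inflated.

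**Simulation of the full score.** Inputs from the article: the score formula, effects coding, 240 people, and eight choice sets ("assuming that each participant will complete eight choice sets"). Assumptions not in the article: six three-level attributes; true ranges 1.2, 0.8, 0.5, 0.3, 0 and 0 (sum 2.8, so true importance 43%, 29%, 18%, 11%, 0% and 0%); two options plus opt-out; a multinomial logit fitted in the group with known membership and no weights.

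| n | mean score of a null attribute | either null above the true 11% attribute |
|---|---|---|
| 240 | about 3% | about 3% |
| 120 | about 5% | about 15% |
| 60 | about 6% | about 34% |
| 34 | about 8% | about 46% |
| 17 | about 10% | about 55% |

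The true 43% attribute averages about 40% at n = 240, 37% at n = 60 and 31% at n = 17. A separate run of the same scenario with random designs gave 19% at n = 120 and 36% at n = 60 for the last column, so these rates are good to a few points. In that run the nulls overtook the true 29% attribute in at most 0.5% of runs at n = 60 to 120, and never the 43% attribute.

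**Other assumptions.** With one null attribute and true ranges 0.3, 0.5, 0.7, 1.0 and 1.4, the mean null score is 2.7%, 5.2%, 6.9% and 8.7% at n = 240, 60, 30 and 17. The null was never exactly zero. It outranked the weakest real attribute in 2%, 25%, 31% and 41% of fits; averaged over all real attributes, the pairwise rate was 0.5%, 7%, 12% and 19%. The chance that it outranks at least one real attribute varies with the scenario:

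| scenario | n=60 | n=30 | n=17 |
|---|---|---|---|
| large effects (weakest range 0.6) | 7% | 22% | 38% |
| two levels | 14% | 35% | 45% |
| base case above | 28% | 42% | 55% |
| four levels | 37% | 49% | 60% |
| small effects (0.2 to 0.6) | 55% | 64% | 73% |

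**Group-size artefact.** In this base case the top attribute's true importance is 1.4/3.9 = 35.9%. Groups with these identical preferences averaged 33.8% at n = 60 and 30.2% at n = 17; the null attribute averaged 5.1% and 9.2%.

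**The case against.** Much can be said for the plan. Range-based importance is one output among several and stands beside the model coefficients. The article does not announce a ranking. Attributes are chosen from interviews and then a ranking exercise with participants, so two attributes of six with exactly no effect is an unfavourable assumption. Cells of 17 need seven classes, and the choice of class number also weighs how people are spread over the classes. The article does not say how sex enters the model; if coefficients are shared across sexes, the unit is a class averaging 34 to 120 people. Intervals and tests may well be in a fuller analysis plan that is not shown. All of this stands, and it limits the size of the problem. The absence of an interval would not by itself be a finding.

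Two stronger readings are also tempting and fail. A reader might infer that sampling error always widens a range. That holds only for a null attribute: in simulation the top attribute's estimated range fell below its true value in 42% to 48% of fits, so for real attributes error goes both ways. A reader might also infer that irrelevant attributes will often outrank real ones in this study. The article gives no attributes, effect sizes or final number of classes from which that could be derived. The confusion is mainly with the weakest attribute, and with all 240 people it is rare (0% to 8%) unless effects are small (25%).

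What remains is the estimator itself. It is written into the article, and an ordinary interval for a share of ranges still lies above zero, so adding one does not remove the bias.

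**Conclusion.** The concern holds in this limited form. The score as fixed gives attributes without effect a positive expected importance, pulls strong attributes down on average, and does both more in smaller groups. Comparisons of importance shares between sex-class groups are therefore partly comparisons of group size. Under the stated assumptions the mean null score is about 3% in the full sample, 5% to 8% at average class sizes (120 to 34) and 6% to 10% at average sex-class cell sizes (60 to 17). Misranking against the weakest real attribute ranges from rare to about half of runs over the same sizes.

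These figures rest on assumed attributes, levels and effects, equal group sizes, known class membership and no weights. Uncertain membership, weighting and unequal classes would generally make the bias larger; shared coefficients across sexes, larger effects or fewer levels would make it smaller. The direction does not depend on these choices. The point is worth correcting before analysis, but it does not undermine the design.

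**What to change.** In the section on attribute relative importance:

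1. Report each score with an interval from draws of the coefficient covariance matrix, or from a bootstrap.
2. Beside it, give the score expected for a null attribute in that cell (the same draws, with that attribute's coefficients centred at zero) and the joint Wald test of its level coefficients.
3. State that scores not distinguishable from the null reference are not ranked as important, without calling those attributes irrelevant. In small cells a failed test may only mean low power.
4. Base comparisons between sex-class groups on level coefficients, or on contrasts specified in advance, with their intervals, and not on raw importance shares. Taking the contrast levels from the full-sample results is less suitable, because it is data-driven and can miss a class that prefers a middle level.

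The cost is a few sentences and a few lines of code, with no change to design or recruitment. The small downside is fewer firm rankings in small cells.

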#### Experimental design

After visual graphics of the attribute levels have been finalised, we will use the software Ngene to develop the experimental design matrix for the DCE pilot.^25^ For the pilot test, no assumptions about the parameter estimates will be made. We will then specify the appropriate number of attributes, levels, alternatives, blocks and choice sets, and Ngene will iteratively generate design matrices of increasing statistical efficiency. We will use the design with the lowest D-error generated by Ngene. An example of a choice set and DCE design is presented in figure 1. Graphics will have alt-text enabled so that they can be accessed by people with visual impairments.

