#### Quality assessment

It is possible that some **participants** known as ‘speeders’ may try to complete the DCE survey as soon as possible without seriously considering the survey questions. ‘Speeders’ will be identified as those who complete the survey at least 50% faster than the median time for survey completion among all valid survey respondents. We will then conduct a sensitivity analysis and determine whether or not the removal of identified speeders significantly alters the results.

We will also assess the possibility of order effect bias by introducing a dummy variable for the order of the choice set. We will test for left and right bias by including a constant for the left choice and examining the extent to which the left position of the alternatives in the choice sets influences the likelihood of being chosen. Comparable probabilities of the left and centre alternatives being selected would suggest the absence of bias.

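### The sentence explaining the predicted opt-out probability describes an odds, exp(V_i)/exp(V_j), and contradicts Equation 2, which it is meant to explain

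*Protocol article*

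**What the plan says.** The section Attribute relative importance and probability of opt-out plans to use Equation 2 to predict how often respondents would choose opt-out "over select sexual health service scenarios for each sex-class combination". The next sentence explains how. It says that "the predicted probability of a participant choosing alternative" i over alternative j can be obtained by "dividing the exponentiated summation of coefficients for scenario" i by the corresponding quantity for scenario j.

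Equation 2 follows. Its numerator is the exponentiated utility of alternative i. Its denominator is a sum of exponentiated utilities indexed by j, with no range printed for the index. Its caption places the prediction "within a two-alternative choice set".

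Two other places bear on which alternatives belong in that sum. Experimental design leaves the design dimensions open: the team will "specify the appropriate number of attributes, levels, alternatives, blocks and choice sets". Quality assessment, on position bias, says: "Comparable probabilities of the left and centre alternatives being selected would suggest the absence of bias".

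**The concern.** The sentence and the equation give different rules for the same quantity. The sentence divides by the term for scenario j alone, while the equation divides by a sum. Because the equation prints no range for its sum, the sentence is the only explanation of the denominator, and it leaves i out.

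Predicted opt-out is a planned output, named in Statistical analysis and again in the title of its own section, and is to be reported for each sex-class combination. An analyst who worked from the sentence would report odds labelled as probabilities. Values above 1 would be noticed. Values below 1 would look plausible and might not be.

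**Working it through.** **Inputs.** The text rule, Equation 2 and its two-alternative caption all come from the section on attribute relative importance and probability of opt-out. The article gives no coefficients and no predicted opt-out probability, so there is no plan figure to reproduce here. The minimum sample size of 191 in Sample size calculation plays no part. The utility differences below are assumptions, chosen to show a range.

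**Notation.** V is the summed coefficients of a scenario, i is opt-out, j is the service scenario, and d = V_i − V_j.

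**Formulas.**
- Text rule: exp(V_i)/exp(V_j) = exp(d).
- Equation 2, two alternatives, sum including i: exp(V_i)/[exp(V_i) + exp(V_j)] = exp(d)/[1 + exp(d)].
- Equation 2 with opt-out against two equally valued services (an assumed three-option scenario): exp(d)/[exp(d) + 2].

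| Assumed d | Text rule | Equation 2, one service | Equation 2, two equal services |
|---|---|---|---|
| −1 | 0.368 | 0.269 | 0.155 |
| −0.5 | 0.607 | 0.378 | 0.233 |
| 0 | 1.000 | 0.500 | 0.333 |
| 0.5 | 1.649 | 0.622 | 0.452 |
| 1 | 2.718 | 0.731 | 0.576 |
| 2 | 7.389 | 0.881 | 0.787 |

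**Direction and size.** The text rule divided by the two-alternative probability is exp(d) ÷ {exp(d)/[1 + exp(d)]} = 1 + exp(d). This is above 1 for every finite d, so the text rule always overstates. The factor is 1 + 0.368 = 1.368 at d = −1, 1 + 1 = 2 at d = 0, and 1 + 2.718 = 3.718 at d = 1. When opt-out is strongly disfavoured the two nearly agree: at d = −3 they are 0.050 and 0.047.

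**Coherence check.** The probabilities of i over j and of j over i must sum to 1. Under the text rule they are exp(d) and exp(−d). At d = 0 they sum to 1 + 1 = 2; at d = 1 they sum to 2.718 + 0.368 = 3.086. Under Equation 2 at d = 1 they sum to 0.731 + 0.269 = 1.

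**The case against.** The strongest defence is that Equation 2 is the named method, is displayed, and is the standard logit form when its sum runs over all alternatives including i. On this view the sentence is a loose verbal gloss, and the harm arises only if the analyst ignores the equation. Most of this stands: the error is one of wording, and nothing shows that the results will be wrong. It does not remove the point, because the sentence is offered as the specific working rule, it is the only explanation of an unindexed sum, and it disagrees with the equation at every finite utility difference.

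A reader might go further and infer that the choice sets contain left, centre and opt-out, so that the two-alternative caption contradicts the design. The article does not establish this. The mention of a centre position suggests a third option, but Experimental design leaves the number of alternatives open and the example choice set in Figure 1 is not available here. Even with three-option tasks, a two-alternative prediction would be legitimate. The stated target is opt-out against a selected service scenario, and a fitted logit can predict for a set of a different size from the one surveyed. The figures of 0.50 and 0.33 at equal utilities answer two different questions; neither corrects the other.

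A reader might also take predicted opt-out to be a headline result. The article does not rank it so; the section presents it as an illustration of heterogeneity in preferences.

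**Conclusion.** The sentence is wrong as written. It defines an odds, calls it a probability, and conflicts with Equation 2. Followed literally, it inflates each predicted opt-out probability by a factor of 1 + exp(d) and gives impossible values whenever d is above 0. The direction needs no assumption about coefficients. The tabulated sizes rest on assumed values of d and, in the last column, on an assumed scenario with two equally valued services.

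The analysis can be recovered from the document, since Equation 2 in its usual reading is correct. What remains is a request for clarity: the article should say which alternatives enter the sum, because the opt-out share depends on whether one service or two are on offer. It should be corrected before the predictions are computed.

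**What to change.** Rewrite the sentence to match Equation 2: the predicted probability of alternative i is exp(V_i) divided by the sum of exp(V) over all alternatives in the scenario, including i. For each predicted scenario, name the alternatives in that sum: opt-out against one service, as the caption has it, or opt-out against two services if the final choice sets have three options and that is the prediction wanted. Adjust the caption if the second is used. Keep the predictions by sex-class combination as planned.

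The cost is a sentence or two of text. Data collection, experimental design, sample size and the fitted models are unaffected.

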### Impact

This study will improve our understanding of older people’s preferences and factors important for sexual health services. Our data will be useful to develop sexual health services and programmes tailored for older people. By engaging older adults, this study will raise awareness for the need to access sexual health services irrespective of age and also ultimately identify strategies co-created by the end-users to increase service uptake.

### Feasibility

Our project is feasible as the team has expertise from multiple disciplines to examine sexual health among older adults with unique strengths in DCEs, disability studies and sexual health research.

### Ethics and dissemination

Ethical approval was obtained from the Research and Ethics Committee at the London School of Hygiene & Tropical Medicine, UK (26134). Findings from this study will be disseminated widely to relevant stakeholders via scheduled meetings, webinars, presentations at conferences and in peer-reviewed journal manuscripts.
